## Intervention

The combined standing desk–healthy messages group (group 1) will be provided with an adjustable sit–stand desk. The desk is designed for placement on top of the participants’ existing workstation, providing the opportunity to transition from sitting to standing without interrupting productivity. Research assistants, qualified in exercise science, biokinetics or physiotherapy, will set up the participants’ workstations in the most appropriate ergonomic position. The correct configuration will therefore be individualised for each study participant. Participants will be visited weekly by the research assistants to examine the set-up, monitor usage and encourage standing-based work. The participants will be asked to break up extended sitting time by accumulating bouts of standing activity, short intermittent bouts of ≥ 10 min initially and then progressing to longer bouts of ≥ 30 min over the course of the intervention (Smith et al. 2017). Regular communication on the benefits of interrupting sitting will be emailed to the participants. The combined standing desk–healthy messages group will also receive health-promoting messages from the authors focussed on lifestyle behaviour modification through email, short message services and telephonic communication once a week during working hours. The participants in the control group (group 2) will continue using their ‘traditional’ workstations as usual.

## Measures

### Phase 1

Data for the RCT will be collected at baseline, 3 months (short term), 6 months (medium term) and 12 months postintervention (long term) using validated measures and standardised assessments.

#### Body composition

Total body weight (kg) will be measured to the nearest 0.1 kg using a calibrated digital weighing scale (Omron HN-288, Hoofddorp, The Netherlands), and standing height will be measured to the nearest millimetre using a calibrated portable stadiometer (Seca 213, Hamburg, Germany). The participants will wear minimal clothing and will not have shoes on during the measurements. Trained student researchers and author 2 will conduct the measurements. Body mass index (BMI, kg/m^2^) will be calculated and classified as underweight (< 18.5 kg/m^2^), normal weight (≥ 18.5 kg/m^2^ and < 25 kg/m^2^), overweight (≥ 25 kg/m^2^ and < 30 kg/m^2^) or obese (≥ 30 kg/m^2^) (American College of Sports Medicine 2017). Using a flexible, but inelastic, measuring tape, a measurement of the waist circumference will be taken at the narrowest part of the trunk, horizontally, whist the participants are standing with arms at the side, relaxed abdomen and feet together (American College of Sports Medicine 2017). Similarly, the hip circumference measurement will be taken at the widest circumference of the proximal thigh, just under the fold of the gluteus, with feet separated slightly (American College of Sports Medicine 2017). Central obesity is defined as a waist circumference ≥ 80 cm for females or ≥ 94 cm for males (Alberti et al. 2009).

#### Blood pressure

The Omron M7 (Intelli IT [HEM-7322T-E], Kyoto, Japan) will be used to record brachial blood pressure (BP). The device has been validated for determining systolic and diastolic BP (El Feghali et al. 2007). Three measurements will be taken after the participant has rested (≥ 5 min) in the seated position with an appropriately sized cuff around the right upper arm, supported at the level of the heart (American College of Sports Medicine 2017). The average of the last two BP measurements will be recorded. Hypertension will be diagnosed as resting systolic BP ≥ 140 mmHg and/or a resting diastolic BP ≥ 90 mmHg, or taking antihypertensive medication. The undiagnosed participants will be advised to seek medical attention.

#### Blood samples

A finger prick test will be used to collect non-fasting capillary blood samples. Random glucose will be measured with the HemoCue Glucose 201RT system (Ängleholm, Sweden), and random total cholesterol, high-density lipoprotein cholesterol and serum triglycerides will be measured with the CardioChek Plus analyser (Polymer Technology Systems, Inc.). The CardioCheck Plus analyser demonstrates good clinical agreement with a reference analyser, ranging from 95% to 98% (Ferreira et al. 2015). Glycated haemoglobin (HbA1c) will be tested using the HemoCue HbA1c 501 system (Pillay et al. 2019). The HemoCue HbA1c 501 system correlates with laboratory HbA1c tests (rho = 0.995; *p* < 0.001). The HemoCue Glucose 201RT system compares with laboratory methods (coefficient of variances < 6.5%) (Kos et al. 2012; Segerhag et al. 2015). A diagnosis of diabetes is considered as having random plasma glucose of 11.1 mmol/L, HbA1c reading ≥ 6.5% or evidence of diabetic medication. Abnormal total cholesterol will be considered as ≥ 4.5 mmol/L or medication for the management of hypercholesterolemia. Participants undiagnosed for elevated total cholesterol or blood glucose will be advised to seek medical attention.

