**Methods/design:**

The protocol will use a mixed-methods study design. Phase 1 of this study is a 12-month, single blinded, randomised controlled trial, which will include baseline, 3-month, 6-month and 12-month post-intervention assessments of plausible cardiometabolic risk biomarkers in office-bound workers at a South African credit and information management company. These biomarkers include anthropometry, sedentary behaviour and physical activity, sleep duration, blood pressure, glucose, glycated haemoglobin (HbA1c), lipid profile and cardiorespiratory fitness. Participants will be randomised into an intervention or control group. The intervention group will be provided with an adjustable sit–stand desk and receive weekly health-promoting messages for the intervention period. Phase 2 will use focus group discussions conducted post-intervention to explore the study participants’ perceptions of the effectiveness of the intervention. Cardiometabolic risk biomarkers and changes in these variables will be compared between the intervention group and the control group at the four time points using descriptive and inferential statistics.

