## Methods

### Study design, setting, participants and selection

This study will use a mixed-methods study design. Phase 1 of the study is a 12-month single-blind randomised controlled trial (RCT). Phase 2 will explore participant perceptions of the effectiveness of the intervention in the workplace.

In the first phase, the study participants will be assigned to an intervention group for 12 months or a control group. They will be randomised into one of two groups: (1) the combined standing desk–healthy messages group or (2) the control group.

The randomisation will be conducted by a qualified biostatistician independent from the core research team.

The potential for contamination will be minimised by adhering to various evidence-based approaches (Magill et al. 2019): (1) participants will be randomised by business unit, (2) participants will be requested not to share details of the intervention, (3) researchers will be asked not to share details of the intervention and (4) a sufficient number of research assistants will be recruited, each allocated to a single business unit. The RCT will be single blinded so that the first and second authors (assessors) are blinded to the group allocation of the study participants.

All adult office workers (18–65 years) from a specific credit and information management company based in Johannesburg (South Africa), working at least 50% of the workday at their desk, 5 days per week, will be invited to participate by the human resources analyst concerned with employee health and wellness through email and telephonic invitations. The inclusion criteria include access to telephone or mobile, email and/or internet and a desk or workstation within the setting; the ability to communicate in English; and the ability to walk or stand for at least 10 min. The exclusion criteria include participants who are pregnant, non-ambulatory or have a diagnosed medical or chronic condition that affects their ability to stand for 10 min or more. Furthermore, participants with other contraindications for working in the standing position and participants not working at the study site will also be excluded from the study. The total current staff complement of the company is 300, and all employees are housed in the same building. The building has three floors, with each respective floor subdivided securely by business unit, thus restricting the movements of staff in the setting.

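### Glucose and triglycerides are specified as random, non-fasting values but serve as repeated between-group outcomes, which adds avoidable meal-related noise and leaves a possible route to bias

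*Protocol article*

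**What the plan says.** The Blood samples section of the protocol article fixes the sampling state: "A finger prick test will be used to collect non-fasting capillary blood samples". It then describes each test in the same terms: "Random glucose will be measured with the HemoCue Glucose 201RT system", and "random total cholesterol, high-density lipoprotein cholesterol and serum triglycerides will be measured with the CardioChek Plus analyser". The section states no time of day, interval since eating or record of the last meal.

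The same section uses glucose and total cholesterol to identify undiagnosed participants. The values are also trial outcomes. The abstract lists glucose and the lipid profile among the biomarkers and says: "Cardiometabolic risk biomarkers and changes in these variables will be compared between the intervention group and the control group at the four time points". Data analysis names change in lipids and change in HbA1c among the regression outcomes; glucose is not in that list.

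Other measures have stated conditions. For blood pressure: "Three measurements will be taken after the participant has rested (≥ 5 min) in the seated position". Weight is taken in minimal clothing without shoes.

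**The concern.** A random sample is one taken without regard to the last meal. That is workable when the question is whether a person needs referral. It is a weak basis for measuring change within a person over 12 months, because glucose and triglycerides move with time since eating. That premise is general knowledge and is not stated in the article.

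Two things are at stake:

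- **Precision.** Each visit adds a meal-related component unrelated to the intervention, and a change score contains two of them. A real effect on triglycerides or glucose becomes harder to see.
- **Bias, conditionally.** Allocation is described as by business unit. If time since eating differed between intervention and control units, and that difference was not the same at follow-up as at baseline, it would appear as a difference in change between arms.

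Nothing described in the article would correct for either afterwards. The diet questionnaire covers habitual intake over the past year, and the beverage questionnaire covers amounts consumed. Neither gives hours since eating at the visit. The regression models look at baseline variables, so they would not capture meal timing at follow-up.

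**Working it through.** **The plan's own figure.** The article claims more than 90% power with at least 60 per group, for sedentary behaviour only. It gives no effect size or SD, so the figure cannot be reproduced. One can only solve for the standardised difference that gives 90% power (two-sided alpha 0.05 assumed, clustering by unit ignored):

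d = (1.960 + 1.282) × √(2/60) = 3.242 × 0.1826 = 0.592.

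This is used below only as a reference point for a glucose or triglyceride outcome.

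**Noise.** If meal timing contributes variance τ² at each visit, independently between visits, a change score gains 2τ². Let f be that addition as a fraction of the variance of change without it. The article gives no value for f, so a range is assumed. Power is Φ(0.592 / (√(1+f) × 0.1826) − 1.960), and the number per arm that restores 90% is 60 × (1+f).

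| f (assumed) | Power | Per arm for 90% |
|---|---|---|
| 0 | 0.90 | 60 |
| 0.25 | 0.83 | 75 |
| 0.50 | 0.75 | 90 |
| 1.00 | 0.63 | 120 |

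This loss does not depend on who takes the blood or on any imbalance between arms.

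**Possible shift, at one visit.** Every input here is an assumption: a post-meal swing of 0.3 to 1.0 mmol/L for triglycerides and 1 to 2 mmol/L for glucose, with 70% of one arm and 30% of the other sampled soon after eating. The false difference at that visit is (0.70 − 0.30) × swing:

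- Triglycerides: 0.4 × 0.3 = 0.12 to 0.4 × 1.0 = 0.40 mmol/L.
- Glucose: 0.4 × 1 = 0.4 to 0.4 × 2 = 0.8 mmol/L.

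**The same shift in change from baseline.** The false difference in change is swing × (imbalance at follow-up − imbalance at baseline). If the imbalance is 0.4 at both visits, the result is swing × (0.4 − 0.4) = 0. If it is 0 at baseline and 0.4 at follow-up, the whole one-visit figure carries through. The figures above are therefore a one-visit illustration and not an expected bias in change.

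**What a shift would do, if there were one.** With no true effect and 60 per arm, a net shift of 0.1, 0.2 or 0.3 SD raises the two-sided false-positive rate from 0.05 to 0.085, 0.195 or 0.376. A shift of the same size against a true effect of 0.592 SD leaves power of 0.77, 0.57 or 0.36. These shift sizes are also assumed.

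**The case against.** The strongest reply is that the article fixes only the random, non-fasting state. Sampling windows and station order are operating detail that a full protocol may hold, and the article does say in general terms that assessments are standardised. This stands in part: silence about a clock-time window does not prove there is none. But random and non-fasting are stated choices, and a general reference to standardisation does not undo them.

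The second reply concerns importance. HbA1c is measured at the same visits, does not depend on the last meal, and is the glycaemic outcome named in Data analysis. The power claim concerns sedentary behaviour and is untouched. Both points stand, and they limit the concern mainly to triglycerides and secondarily to glucose.

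A reader might infer a stronger version, namely that meal timing is tied to arm by design. The article says "participants will be randomised by business unit" and that "a sufficient number of research assistants will be recruited, each allocated to a single business unit", so assistants appear nested in arm. The documents do not carry the argument further:

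- No section says that these assistants take or schedule the finger pricks. Their stated tasks are desk set-up, weekly visits and the step-test heart rate.
- The one-unit rule is given as a measure against contamination, and "the first and second authors (assessors) are blinded to the group allocation of the study participants".
- The number of business units is not given, so it cannot be said that an imbalance would fail to average out.

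A reader might also suppose that intervention participants reach the finger prick straight from standing. Nothing in the article says so, and it offers no size for such an effect.

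**Conclusion.** The point holds in a limited form. As described, random non-fasting triglycerides and glucose are suited to screening but are needlessly noisy measures of change, and no described item or model removes the noise. Its size cannot be taken from the article. If timing adds 25% to 100% to the variance of change, power for an effect otherwise detectable at 90% falls to between 0.83 and 0.63.

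Bias between arms is a risk and is not shown. It requires sampling times relative to meals to differ between arms and, for change from baseline, to differ otherwise at follow-up than at baseline. The 0.12 to 0.40 and 0.4 to 0.8 mmol/L figures illustrate one visit under assumed inputs and should not be read as estimates.

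Total and HDL cholesterol are less of a concern, and HbA1c is not affected by the last meal. This is a cheap improvement worth making; it does not undermine the trial's main comparison.

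**What to change.** Keep non-fasting finger-prick samples and make these changes:

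1. Sample each participant in the same clock-time window at baseline, 3, 6 and 12 months, with the windows balanced across intervention and control units.
2. Record hours since the last food or sweet drink at each visit.
3. Adjust the triglyceride and glucose comparisons for that recorded interval.
4. State that the glycaemic conclusion rests on HbA1c, with random glucose kept for screening.

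If the full protocol already sets such a window, a sentence saying so under Blood samples covers the first item.

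The cost is slightly less flexible appointments and one more recorded item per visit. No extra test or staff is needed.

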#### Accelerometry

The small, lightweight and wrist-worn Axivity accelerometer, version AX3 (Newcastle-upon-Tyne, United Kingdom) will be used to collect free-living sleep, sedentary behaviour, light physical activity and moderate-to-vigorous physical activity data. The AX3 has been used in large-scale surveillance studies such as the UK Biobank study (Doherty et al. 2017). This wrist-worn monitor shows excellent agreement with the gold standard doubly labelled water for estimating total energy expenditure (rho = 0.90 and *p* < 0.05 in the dominant wrist; rho = 0.91 and *p* < 0.05 in the non-dominant wrist) (White et al. 2019). The AX3 will be initialised to capture triaxial acceleration data at 100 Hz with a dynamic range of ± 8 g. Participants will be asked to wear the device on their wrist during all hours of the day, over a period of 7 days, except for water-related activities that are not considered as water resistant (e.g. bathing and swimming). Data processing and analysis methods are described elsewhere (Doherty et al. 2017). Data captured by the AX3 will be processed and analysed using an open-source software project developed and used by the UK Biobank Study (https://github.com/activityMonitoring/biobankAccelerometerAnalysis) and the Open Movement AX3 open source software (OmGui version 1.0.0.39, Newcastle University, Newcastle upon Tyne, United Kingdom).

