## Introduction

The global impact of preventable cardiometabolic and non-communicable diseases remains excessively high; however, low- to middle-income countries (LMICs) such as South Africa bear the greatest burden (World Health Organization 2018). Insufficient physical activity is still the main behavioural risk factor driving the increase in preventable diseases in South Africa. The demands on employee productivity are high, resulting in prolonged sedentary behaviour, particularly amongst clerical workers (Clemes et al. 2014a). Sedentary behaviour is defined as ‘awake’ activities with limited energy expenditure, while in a sitting, reclining or lying posture (Tremblay et al. 2017). Continuous time in sedentary activities is associated with increased risk of cardiometabolic diseases and inflammatory markers, independent of moderate-to-vigorous physical activity (Hadgraft et al. 2020). Domains of sedentary behaviour include time spent sedentary during occupation, transport and outside of working hours (Clemes et al. 2014b). Workers in office-bound occupations are at an increased risk of being sedentary for most of the occupation-related domain (Chau et al. 2010). A study demonstrated that employed individuals use motorised transport for an average of 0.63 ± 0.68 h/day (Clemes et al. 2014b). This study demonstrated that participants who sat for more than 80% of the workday had higher sitting times during motorised commuting compared with those who sat for < 58% of the workday (1.07 ± 0.98 hours per day vs. 0.35 ± 0.27 hours per day, respectively; *p* < 0.0001) (Clemes et al. 2014b). The adult working population in high-income countries has been found to accumulate sedentary behaviour whilst at work, during recreational time at home and during travel time (Chau et al. 2010). Compounded by sedentary activities outside of work, this accumulated sedentary behaviour may increase the risk for cardiovascular disease, type 2 diabetes and all-cause mortality beyond certain thresholds, even adjusting for physical activity (Patterson et al. 2018). Even in LMICs, worker productivity is becoming increasingly reliant on technology-based solutions with little need to move from the seated position for any tasks, which encourages sedentary behaviours (Gradidge 2017). The implications include limited employee productivity, mental health concerns, financial strain and increased absenteeism. It is therefore important to address sedentary behaviour in the workplace.

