#### Tools

Participants will be asked to complete an appropriate questionnaire to identify self-reported sociodemographic characteristics (age, salary band, position in the company, highest level of education and smoking status), sedentary behaviour, diet and beverage consumption, mental health and absenteeism.

Self-reported sedentary behaviour in the previous 7 days will be quantified using the Last 7 Days Sedentary Time Questionnaire (SIT-Q-7d). The questionnaire includes self-reported sedentary time in five main domains as well as sleep and nap time. The domains include sedentary time during meals, travel, work, recreation and during other non-specified sedentary time. The SIT-Q-7d is acceptable for use in epidemiological studies, with criterion validity for domain-specific variables ranging from 0.22 to 0.76 (Wijndaele et al. 2014).

Habitual consumption of vegetables, fruit, whole grains, dairy, meats and poultry over the past year will be determined using a self-reported dietary intake questionnaire (Kolbe-Alexander et al. 2008). A beverage intake questionnaire (BEVQ-15) quantifies the amount of unsweetened beverages, sugar-sweetened beverages and alcohol consumed by the participants, with validity between 24-h food item recall and BEVQ-15 ranging from rho values of 0.69 to 0.76 (*p* < 0.001) (Hedrick et al. 2012). The estimated number of kilocalories per drink will be calculated.

The Centre for Epidemiological Studies Depression Scale (CES-D-10) is a validated questionnaire (rho = 0.81–0.94, *p* < 0.05 [Baron, Davies & Lund 2017]) that estimates the mental health status of employees, specifically eliciting symptoms of depression in the past 7 days (Andresen et al. 1994). The tool includes items on the effect of depression, somatic symptoms and positive effects. A four-point Likert scale is used for each item, ranging from ‘rarely or none of the time’ to ‘all of the time’.

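### The wrist accelerometer is not shown to tell sitting from standing, so a null device result would not show that the sit–stand desk left sitting unchanged

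*Protocol article*

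**What the plan says.** - **Construct.** The Introduction defines sedentary behaviour as waking activity "with limited energy expenditure, while in a sitting, reclining or lying posture". Posture is part of the definition, so quiet standing is not sedentary.
- **Intervention.** The desk sits on the existing workstation, "providing the opportunity to transition from sitting to standing without interrupting productivity". Participants are asked to "break up extended sitting time by accumulating bouts of standing activity". Weekly health messages and regular emails about interrupting sitting are added.
- **Device measure.** Under Accelerometry, sedentary behaviour is one of the outputs of the "small, lightweight and wrist-worn Axivity accelerometer, version AX3", alongside sleep and physical activity. The device is worn at all hours for 7 days, and data processing is referred to a cited source. The validity statement is that the monitor "shows excellent agreement with the gold standard doubly labelled water for estimating total energy expenditure" (rho 0.90 and 0.91 for the two wrists).
- **Questionnaire measure.** Under Tools, the SIT-Q-7d records self-reported sedentary time: "The domains include sedentary time during meals, travel, work, recreation and during other non-specified sedentary time". Its criterion validity by domain is given as 0.22 to 0.76.
- **Power and analysis.** The sample-size paragraph claims more than 90% power at 60 per group for a difference in sedentary behaviour. Data analysis lists change in sedentary behaviour as an outcome. Neither says whether this means the AX3 or the SIT-Q-7d.

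**The concern.** The trial defines its target by posture and intervenes on posture, but its device records acceleration at the wrist. A person typing while standing is not sedentary by the article's own definition, yet the wrist may move much as it does when that person types seated. Nothing in the article shows that the wrist output separates the two.

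If some standing desk work is scored as sedentary, the error falls mostly on the arm that was given the desks. The device-based difference between groups then shrinks. A null AX3 result could mean that the desks did not reduce sitting, or that the wrist did not register the reduction, and the device data alone could not tell these apart.

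This matters because sedentary behaviour is the only outcome with a power statement, and a posture-valid device measure would have been the natural check on self-report from participants who know their allocation.

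**Working it through.** **1. The statements side by side**

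| Element | What the article fixes | Does it involve posture? |
|---|---|---|
| Definition (Introduction) | Low energy expenditure and sitting, reclining or lying | Yes |
| Intervention | Sitting replaced by standing during desk work | Yes |
| AX3 (Accelerometry) | Triaxial acceleration at the wrist; validity for total energy expenditure | Not shown |
| SIT-Q-7d (Tools) | Self-reported sedentary time, including a work domain | Sedentary time is asked about, not observed |
| Powered outcome (sample size) | Sedentary behaviour, measure not named | Cannot be determined |

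**2. The plan's own figure**

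The article gives no effect size, standard deviation or drop-out rate, so its power cannot be reproduced forwards. Working backwards, with 60 analysed per arm, independent participants, two-sided 0.05 and exactly 90% power:

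d = (z₀.₉₇₅ + z₀.₉₀) × √(2/60) = (1.960 + 1.282) × 0.1826 = 0.592

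Using the t distribution the value is 0.597. Because the article says more than 90%, the intended effect would be at least this large.

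**3. Illustration: part of the effect is not registered**

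Let r be the share of the true standardised effect that the measure retains. Then power ≈ Φ(3.242 × r − 1.960). The shares are assumptions; the article gives no misclassification rate.

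| Share missed (assumed) | r | Power at 60 per arm | Per arm for 90% |
|---|---|---|---|
| 0% | 1.00 | 90% | 60 |
| 25% | 0.75 | 68% | 107 |
| 50% | 0.50 | 37% | 240 |
| 75% | 0.25 | 13% | 960 |

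A larger planned effect would be hurt less. With d = 0.8, power at 60 per arm is 99%; missing half leaves d = 0.4 and 59%.

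**4. Illustration: averaging over the week**

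Eligible staff are "working at least 50% of the workday at their desk, 5 days per week". If the desk changes sitting only on workdays and the outcome is a 7-day daily mean, the difference in minutes is multiplied by 5/7 = 0.714. A change of 60 minutes per workday becomes 60 × 5/7 = 43 minutes per day. With an unchanged standard deviation (assumed), power falls from 90% to Φ(3.242 × 0.714 − 1.960) = 64%. This applies only if the 7-day mean is the analysed quantity, which the article does not say.

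**The case against.** Several points on the other side are sound.

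- **The powered outcome is not tied to the AX3.** A reader might infer that the outcome behind the sample size is itself biased. The documents do not support that, because the sample-size and analysis text name no measure and the SIT-Q-7d also quantifies sedentary behaviour. The point about a null result therefore concerns the AX3 alone.
- **Work sitting is not wholly unmeasured.** The SIT-Q-7d has a work domain. It is only a partial safeguard: only the assessors are blinded, so participants who know their group report their own sitting, with stated validity as low as 0.22.
- **Wearing the device all week does not fix the analysis window.** Round-the-clock wear is needed for sleep, working hours can be cut out later, and a condensed article may leave that to the full protocol. The messages may also act outside work. The lack of a stated working-hours window is thus no error.
- **Dilution is easily overstated.** With an assumed 8-hour workday and 16 waking hours a day, work is 40 of 112 waking hours (36%), and a reader might infer that the effect shrinks to about a third. It does not: minutes no longer spent sitting at work stay in the day's total, whatever else that day holds. Averaging over the week costs at most the 5/7 factor in minutes.
- **Misclassification is plausible, not demonstrated.** The classification method is in a source not at hand, and the article has no data on wrist movement seated versus standing. Any extra walking would register at the wrist.

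The mismatch survives these points: the article offers no evidence that its device measures the posture on which its definition and intervention rest. A later analysis plan cannot recover posture that was never recorded.

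**Conclusion.** The concern holds for the device measure. Sedentary behaviour is defined and targeted as posture, while the only device output called by that name comes from a wrist sensor whose cited validity is for energy expenditure. Standing desk work may be counted as sedentary in the intervention arm. Such an error would push the AX3 difference towards zero, so a null AX3 result should not be read as unchanged sitting.

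The size of the loss cannot be derived from the documents. The figures of 68%, 37% and 13% rest on assumed shares missed, an effect back-solved from exactly 90% power, 60 analysed per arm and independent participants. The 64% figure rests on a workday-only change, a 7-day mean and an unchanged standard deviation. The direction depends only on some standing desk work being scored as sedentary.

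It would go too far to say that the trial cannot detect its main effect, or that its power claim is wrong for this reason. The questionnaire covers work sitting, and the measure behind the power claim is not stated.

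**What to change.** 1. Report the wrist AX3 output as low-movement time. Do not interpret it, or a null result on it, as sitting time.
2. Use the AX3 time stamps to analyse working hours on workdays separately from the whole-week result.
3. Report SIT-Q-7d work-domain sitting beside it as the posture-related measure, stating that it is self-reported by participants who know their group and has validity of 0.22 to 0.76.
4. State which measure the power of more than 90% refers to.

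All of this uses data already planned. The cost is a little more analysis and a narrower claim from the device.

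Wearing the same AX3 on the thigh, where its angle could separate sitting from standing, is an option only if the sponsor accepts losing the wrist-based sleep and activity pipeline. It would have to be settled before data collection. Making the SIT-Q-7d the sole sitting outcome is not clearly better, since unblinded self-report could bias the result towards a false effect.
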